### Tertiary Outcomes: Engagement With Types of Tips

Another outcome of this experiment is to determine what types of tips are most engaging (directive, social proof, or present bias tips). We will assess this by comparing engagement with the tips in arm 2 and arm 3 via a 1-way ANOVA in which the types of tips are used as the independent variable. We will then assess if age and gender predict which type of tip is the most engaging by using multiple regression.

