### Intervention Groups

Members allocated to the first arm will be presented with a member home page that contains no behavioral prompts. Figure 3 is a screenshot of an arm 1 homepage for a member who chooses to engage with the depression course.

Members allocated to the second arm will be presented with a member page that contains a *Tip-of-the-Day* section containing directive content. The randomization strategy for the 35 directive tips is randomization without replacement. Figure 4 is a screenshot of an arm 2 homepage for a member who chooses to engage with the depression course.

Members allocated to the third arm will be presented with two sections that contain interactive prompts. The first is a *Tip-of-the-Day* section containing social proof and present bias content. At each log in, members will see a new tip. The randomization strategy for the tips is randomization without replacement. There are 15 social proof tips and 15 present bias tips.

In addition to the tips of the day, the third arm will also feature a to-do checklist that lists interactive course components. When a member clicks on an interactive component, they will be brought to the exercise. When they complete the exercise, the item is marked as complete with a check mark. Figure 5 is a screenshot of an arm 3 homepage for a member who chooses to engage with the depression course.

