### Data Collection

Evolution Health developed a custom data collection interface and reporting mechanism. Data will be collected for each member who is randomized into the experiment. Data on age and gender will be collected at registration or at secure sign-on in various white-label versions. The course components that will be promoted by the tips and to-do items are listed in Table 4.

The following behaviors are tracked in the custom database for each tip and to-do item that is randomly presented to a user: whether a tip was shown, whether a tip was clicked on, and whether a user completed the course component described in a tip or to-do item.

It is possible for a single member to participate in both courses. However, the study was designed to test behavioral economics prompts, not courses. Participants will be randomized to an intervention arm in which behavioral nudges and prompts are consistent across courses.

**Table 4 table4:** Course components tracked for engagement.

Action code	Course component
1^a^	Uploading a personal image to their profile
2^a^	Completing cognitive behavioral therapy session 1
3^a^	Use of the program’s diary
4^a^	Read a community post
5	Review another member’s profile
6	Posting in the community
7^a^	Review a course worksheet
8^a^	Set personal goals
9	Read other members’ goals
10^a^	Complete the depression and anxiety test
11^a^	Watch the *Getting Started* video
12	Give a community member a thumbs-up
13	Encourage a community member by clicking their “show support” icon
14	Private message a community moderator

^a^Item in the to-do checklist.

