### Primary Outcome: Engagement With Tips and To-do Items

We will first measure engagement with the tips and to-do items in arms 2 and 3. We will compare the frequency of engagement with each nudge and behavioral prompt by age and gender. A member’s engagement with tips will be measured as the proportion of tips that were clicked. Specifically, it will be a value between 0 and 1, calculated as the number of tips that a member clicked divided by the number of tips that were presented to the member. Engagement with to-do items will be measured as the number of to-do items that a member clicked, and course component completion rates will be measured as the number of course components that a member completed. All comparisons between arms 2 and 3 will be conducted by using an independent sample 1-tailed *t* test; a conventional α level (.05) for statistical significance will be used.

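### Tip type is fully tied to the to-do checklist in arms 2 and 3, so the secondary and tertiary ANOVAs cannot support a ranking of directive against social proof and present bias tips

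*Protocol article*

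**What the plan says.** All references are to the Protocol article.

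- **Arms (Intervention Groups).** Arm 2 has a Tip-of-the-Day "section containing directive content. The randomization strategy for the 35 directive tips is randomization without replacement". Arm 3 has a Tip-of-the-Day "section containing social proof and present bias content. At each log in, members will see a new tip", and "There are 15 social proof tips and 15 present bias tips". The same section adds: "In addition to the tips of the day, the third arm will also feature a to-do checklist that lists interactive course components". Clicking a checklist entry takes the member to the exercise. Arm 1 has neither element.
- **Targets (Data Collection, Table 4).** Tips and to-do items draw on one list of 14 components. The footnote "Item in the to-do checklist" marks eight of them: codes 1, 2, 3, 4, 7, 8, 10 and 11.
- **Primary outcome.** "A member’s engagement with tips will be measured as the proportion of tips that were clicked". To-do clicks and completed components are measured separately. Arms 2 and 3 are compared by a 1-tailed t test at .05, and the direction is not given.
- **Secondary outcome.** Completion in arms 2 and 3 is compared by a 1-way ANOVA with tip type as the factor.
- **Tertiary outcome.** The aim is to find which of the three tip types engages members most. The stated method is "comparing engagement with the tips in arm 2 and arm 3 via a 1-way ANOVA in which the types of tips are used". Tip type is the only factor.

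Strengths and Limitations does not mention that tip type and checklist go together.

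**The concern.** Arms 2 and 3 differ in two things at once, the wording of the tips and the presence of the checklist, but the secondary and tertiary models name only the first.

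The checklist could plausibly move both outcomes. It offers another route from the home page to 8 of the 14 components that the tips promote. A member who takes that route has less reason to click a tip for the same component, yet the tip shown still counts in the denominator of the click proportion. The checklist could equally raise general activity, tip clicks included. For completion the link is more direct, because checklist entries lead to the components being counted.

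The stake is the trial's message. The abstract's conclusions expect to learn which kinds of prompt and nudge work best, and Future Directions says the secondary and tertiary outcomes will shape later nudges and customized content. A finding that directive tips do better, or worse, than the other types could be entirely a checklist effect.

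**Working it through.** **1. The plan's own figure.** Power and Sample Size gives 1414 per group for 0.95 power at .05, with 3.14% and 5.79% (printed as power, but matching 16/510 and 28/484, so read as completion proportions). The one-sided two-proportion formula gives 1313. With the continuity correction, n/4 × [1 + √(1 + 4/(n × 0.0265))]² at n = 1313 gives 1387, which is 27/1414 = 1.9% below the stated figure. The sample size is not at issue here. 1414 is used below only as the planned arm size.

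**2. Cells and parameters.** Let m be the mean for directive tips without the checklist, s and p the content effects of social proof and present bias relative to directive, and c the checklist effect.

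| Tip type | Arm | Checklist | Mean |
|---|---|---|---|
| Directive | 2 | no | m |
| Social proof | 3 | yes | m + s + c |
| Present bias | 3 | yes | m + p + c |

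The design matrix has four columns (intercept, social proof, present bias, checklist) and rank 3. The contrasts are:

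- social proof − directive = s + c
- present bias − directive = p + c
- social proof − present bias = s − p

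Only the last is free of c. More members narrow the interval around s + c but do not separate its parts. Arm 1 does not help: it shows no tips, so it has no tip-click outcome. For completion it supplies a baseline but also brings in a further unknown, the effect of directive tips against none.

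**3. Illustration for the tertiary ANOVA.** Assume s = p = 0 and let the checklist shift tip clicking by d SD in either direction. The documents give no value for d, so a range is shown. The noncentrality is λ = Σ nᵢ(μᵢ − μ̄)². With 1414/707/707 units, λ = 707d². With 1414 in each group, λ = 942.7d². Units are treated as independent, which is a simplification because an arm 3 member can see both tip types.

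| d (SD) | λ | Chance of p < .05 with no content effect |
|---|---|---|
| 0 | 0 | 5% |
| 0.05 | 1.77 to 2.36 | 20% to 26% |
| 0.10 | 7.07 to 9.43 | 66% to 79% |
| 0.15 | 15.9 to 21.2 | 96% to 99% |
| 0.20 | 28.3 to 37.7 | about 100% |

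**4. The same shift in the primary test.** If the 1-tailed test looks for arm 3 > arm 2, the rejection probability is Φ(d√(1414/2) − 1.645): 37.6% at d = 0.05, 84.5% at d = 0.10, and about 0.1% or less at d = −0.05 or −0.10. These rejections are errors only if the result is read as a tip-content effect. As a difference between the two home pages they are correct.

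**5. A click-diversion scenario.** Assume a 10% click chance per tip, one tip per member, tips spread evenly over the 14 components, and a share q of would-be clicks on the eight checklist components going to the checklist. The arm 3 rate is 0.10 × (1 − (8/14)q), which is 8.6% at q = 0.25 and 7.1% at q = 0.50. With 1414 per arm, z = 1.31 and 2.72. A 1-tailed .05 two-group test looking for arm 2 > arm 3 rejects 37% and 86% of the time.

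**The case against.** A reader might infer that the primary test is invalid too. The documents do not support that. The primary section measures tips and to-do items separately, compares randomized arms and does not name tip content as the cause. Practical Implications ties the decision to whole home pages, since the arm 2 or the arm 3 page would become the default. For that purpose a package comparison is the right one.

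The secondary aim is also broader than its model. It asks whether presenting tips and to-do items raises completion, so the checklist is part of the declared intervention. The fault there is the factor label.

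A reader might also suppose that arm 2 members can reach a component only through a tip. Arm 1 has neither tips nor checklist, yet the early subsample figure for it is 3.14%, evidently session completion. Other routes exist.

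The 37% and 86% should not be taken as estimates. The click rate, diversion shares and even spread are assumptions. One tip per member does not fit a new tip at each log in. The test direction is not stated, and the calculation is a two-group test rather than the planned three-level ANOVA. The checklist might also raise tip clicking.

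These points narrow the concern. They leave the structure of the secondary and tertiary models untouched: neither a larger sample nor more analysis detail can separate two things that never vary independently.

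**Conclusion.** The concern holds for the secondary and tertiary analyses. Contrasts of directive tips with the other two types estimate content plus checklist, so the three-way ranking, and any completion difference attributed to tip type, has no support at any sample size. This follows from the arm definitions alone and needs no numerical assumption. The size and sign of the bias are unknown. The figures above show only that, at the planned size, a modest checklist effect would often produce a significant result with no difference in content.

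The primary comparison is sound as a contrast of two home-page packages and should be read only that way. Social proof versus present bias is not confounded with checklist presence, because arm 3 members have the checklist for both. That contrast still assumes the two sets of 15 tips target similar components, which the article does not show.

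**What to change.** Data collection ended in May 2022 (Results), so a factorial arrangement of tip type by checklist is no longer available to this trial. The changes are to the analysis wording and the reporting:

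1. Draw conclusions on tip content only from social proof versus present bias within arm 3, with an analysis that allows for the same member seeing both types.
2. Describe arm 2 versus arm 3 differences in tip clicks and in completion as package effects: directive tips alone against social proof and present bias tips plus checklist. Remove tip type as the stated cause in the secondary and tertiary sections.
3. Add the confounding to Strengths and Limitations.
4. Optionally, repeat the arm 2 versus arm 3 tip-click comparison on tips for the six components not on the checklist (codes 5, 6, 9, 12, 13 and 14), as a sensitivity analysis only. It removes direct link competition but not other effects of the checklist, such as on attention or on how often members log in. Most of these components are community features, and Strengths and Limitations says that some community tools are not used by all white-label clients.

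The cost is some rewording and, if wanted, one extra analysis of data already logged on fewer tips. The real loss is that the three-way ranking of tip types can no longer be claimed.

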### Secondary Outcomes: Completion of Course Components

A secondary outcome of this experiment is to test whether the presentation of tips and to-do items increases the overall completion of course content. We will achieve this by comparing course component completion rates in arm 2 and arm 3 via a 1-way ANOVA in which the types of tips are used as the independent variable. We will then assess if age and gender predict which type of tip is the most engaging by using multiple regression.

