### Future Directions

Although the content is different, the platform’s addiction courses have user home page interfaces that have the exact same layout as that of the arm 1 home page interface. If the results from our study indicate that members engage with the prompts and nudges in arm 2 and arm 3, we will replicate this experiment with new members who register for these courses. Although the addiction courses focus on problem drinking and smoking cessation, the use of nudges and prompts to increase engagement may be generalizable to many digital health courses that focus on addictions and mental health.

The secondary and tertiary outcomes will help shape the development of future nudges and prompts. If specific types of nudges and prompts are appealing to specific gender and demographic groups, we will customize the content for these groups and analyze their effectiveness in future studies.

We are currently employing natural language processing to analyze identifiable contexts (ie, change talk) in our communities [52]. We will apply the findings from that experiment to the member-generated content from the goals and diary tools to better determine the types of prompts and nudges that result in engagement among members. The overall goal will be to use artificial intelligence to train the platform to recognize different usability patterns and show specific engagement prompts and nudges to stratified populations.

The goal of the courses is to promote wellness and increase access to efficacious, self-guided support for people with depression and anxiety. The focus of the study is restricted to testing whether nudges and prompts increase engagement. If the study is successful, future research will need to determine if nudges and prompts contribute to decreases in depression and the frequency and intensity of panic attacks.

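### The three tip types are compared by a 1-way ANOVA, although social proof and present bias tips go to the same arm 3 members, so two of its three groups are not independent

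*Protocol article*

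**What the plan says.** Members are randomised to arms, not to tip types (Randomization). Under Intervention Groups, arm 2 shows 35 directive tips only. For arm 3, "The first is a *Tip-of-the-Day* section containing social proof and present bias content", and "There are 15 social proof tips and 15 present bias tips". A new tip appears at each log in, drawn without replacement. Arm 3 alone also has the to-do checklist.

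The section on tertiary outcomes names directive, social proof and present bias tips as the types to be ranked and plans "comparing engagement with the tips in arm 2 and arm 3 via a 1-way ANOVA in which the types of tips are used", so that tip type is the factor. It continues: "We will then assess if age and gender predict which type of tip is the most engaging by using multiple regression".

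The section on secondary outcomes applies the same factor to a different outcome. Its method is "comparing course component completion rates in arm 2 and arm 3 via a 1-way ANOVA in which the types of tips are used", so tip type is the factor here too, and the section then repeats the age-and-gender sentence about tip engagement word for word.

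The primary outcome section defines tip engagement as one proportion per member over all tips presented, and completion as one count per member. Data Collection says that, for each tip, the database records whether it was shown, whether it was clicked, and whether the component it described was completed. The article mentions no member effect, pairing or clustering.

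**The concern.** A 1-way ANOVA compares groups made up of different, independent units. Directive against the rest is such a comparison, because it is arm 2 against arm 3. Social proof against present bias is not: both types come from the same arm 3 members. Someone inclined to click will tend to click both kinds, so the two group means are positively correlated and the test's standard errors no longer match the design.

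The comparison that suffers most is also the cleanest one in the trial. Within arm 3, tip type is assigned at random and every member has the checklist, so social proof against present bias is free of the arm difference. The planned test discards the precision that this arrangement offers.

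The same factor is used for completion. A single count per member has no one tip type for an arm 3 member who saw both.

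The results are meant to be used: "If specific types of nudges and prompts are appealing to specific gender and demographic groups, we will customize the content for these groups". That is a question of whether the effect of tip type differs by age or gender, and the plan should say so.

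**Working it through.** **Figures in the plan.** The article gives no figure for these ANOVAs, so there is none to reproduce. The 1414 per group from Power and Sample Size is used only to size the simulation.

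**Inputs.** From the article: three tip types, two of them shown to the same members; 15 + 15 tips in arm 3; one new tip per log in. Assumed, because the article does not give them: within-member correlation ρ of 0.3 to 0.7 between the two arm 3 click rates, equal variances, equal arms of size n, and all 30 arm 3 tips equally likely to be drawn.

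**1. How many arm 3 members see both types.** After k log ins, P(both) = 1 − 2·C(15,k)/C(30,k).
- k = 1: 0
- k = 2: 1 − 2·105/435 = 52%
- k = 3: 1 − 2·455/4060 = 78%
- k = 5: 1 − 2·3003/142506 = 96%

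**2. Type I error with full overlap (every arm 3 member has seen both), nominal two-sided 5%.**
- Social proof vs present bias: assumed variance 2/n, true variance 2(1−ρ)/n, ratio w₁ = 1−ρ. Error = 2[1 − Φ(1.96/√w₁)].
- Directive vs the mean of the two arm 3 types: assumed 1.5/n, true [1 + (1+ρ)/2]/n, ratio w₂ = (3+ρ)/3. Error = 2[1 − Φ(1.96/√w₂)].
- Overall F: in large samples 2F behaves as w₁X₁ + w₂X₂, with X₁ and X₂ independent chi-square on 1 df, against the critical value 5.991. Since w₁ + w₂ = 2 − 2ρ/3 is below 2, the statistic is too small on average.

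| ρ | w₁ | w₂ | Social proof vs present bias | Directive vs arm 3 tips | Overall F |
|---|---|---|---|---|---|
| 0.3 | 0.70 | 1.10 | 1.9% | 6.2% | 3.8% |
| 0.5 | 0.50 | 1.17 | 0.6% | 7.0% | 3.4% |
| 0.7 | 0.30 | 1.23 | 0.03% | 7.8% | 3.3% |

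A null simulation with 1414 per arm and 2000 replicates agrees. At ρ = 0.3 it gave 1.5%, 6.4% and 3.6%; at ρ = 0.5 it gave 0.7%, 7.4% and 3.3% (same column order).

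**3. Partial overlap.** Let a fraction f of arm 3 members see both types and the rest split evenly. The correlation between the two group means becomes κ = 2fρ/(1+f), with w₁ = 1−κ and w₂ = 1 + κ/(2+f). For f = 0.25 (an assumption), κ = 0.4ρ, so κ is 0.12 at ρ = 0.3 and 0.28 at ρ = 0.7. The errors over that range are:
- social proof vs present bias: 3.7% to 2.1%
- directive vs arm 3 tips: 5.6% to 6.5%
- overall F: 4.5% to 4.1%

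**4. Simulation of log ins and clicks.** This assumed a mean click rate of 10%, an intra-member correlation of 0.3 to 0.5 and a mean of 1.5 to 6 log ins, with tips drawn from the 15 + 15 pool. Between 21% and 73% of arm 3 members saw both types. The overall F had an error of 3.7% to 4.3%, and social proof vs present bias 0.3% to 3.4%.

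**The case against.** Several stronger readings are tempting, and the article does not support them.

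- **That every arm 3 member sees both types.** A member who logs in once sees one tip and so one type. Log in counts are not given, and the Introduction describes poor adherence as usual in the field. The full-overlap figures are therefore an upper bound on the distortion at a given correlation.
- **That the planned test produces excess false positives.** The named test is the overall F, which is mildly conservative. The 6.2% to 7.8% belongs to a directive-against-pooled-arm-3 contrast. The article names no follow-up contrasts, and an article may leave these to the full plan. Inflation arises only if that contrast is made with the ANOVA's standard error.
- **That the completion ANOVA is impossible.** Unlike the tertiary section, the secondary section does not list three types. Read as directive content against arm 3 content, its factor is simply the randomised arm: each member belongs to one group and the test is valid. What stands is that "1-way ANOVA in which the types of tips are used as the independent variable" is the wrong label for that comparison, since the arms also differ by the checklist, and that the three-level reading would not work.
- **That the regression tests only main effects of age and gender.** The article does not state its terms, so this cannot be inferred. What stands is that the tailoring question needs type-by-age and type-by-gender terms. The article also says that the effectiveness of tailored content would be analysed in future studies.

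It is also fair to say that the primary arm 2 against arm 3 t test is unaffected. None of this removes the core point: with three named types, two of the groups share members, and the stated test does not allow for it.

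**Conclusion.** The point holds for the tertiary analysis. A 1-way ANOVA over the three tip types does not fit a factor that varies within arm 3 members. The harm is mainly lost power. The overall F runs at about 3.8% to 3.3% instead of 5%, and social proof against present bias at 1.9% to 0.03%, given full overlap, equal variances and ρ of 0.3 to 0.7. With less overlap all the figures move towards 5%. The article gives neither the overlap nor the correlation, so the direction is firm for any positive correlation, but the size is not.

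For the secondary analysis the defect is one of wording: the factor is misnamed, and the regression sentence concerns a different outcome. Severity is moderate, confined to secondary and tertiary outcomes.

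**What to change.** **Tertiary outcomes.** Replace the 1-way ANOVA with a logistic GEE or logistic mixed model on tip impressions (shown, clicked yes/no), clustered on member. Tip type is a fixed effect, and type-by-age and type-by-gender terms (with age and gender themselves) address tailoring. Report social proof vs present bias as the contrast within arm 3. Report directive vs arm 3 tips separately as a between-arm contrast, and state that it is confounded with the to-do checklist, which only arm 3 has. No model removes that confounding.

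**Secondary outcomes.** Name randomised arm, not types of tips, as the factor for the completion count. Delete the tip-engagement regression sentence repeated from the tertiary section.

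**Cost.** A little more analysis work. The tip-level records already exist according to Data Collection, so no new data are needed and the primary analysis does not change.
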